**Inclusion criteria:**

The study will include a convenience sample of seniors of both sexes above 60 years of age, with a cognitive level that is adequate to understand the evaluations and interventions of the study. The subjects will be recruited from the geriatric outpatient clinic of the University Hospital of the Federal University of Juiz de Fora (HUCAS/UFJF), and will be invited through posters that will be put up to publicize the study, and/or by invitation of the researcher in the waiting room during their visits to the outpatient clinic.

**Exclusion criteria:**

Elderly people with cognitive changes detected on the basis of cutoff score < four on the Six Item Screener (ANNEX I) proposed by Callahan et al. (2001), presence of an inflammatory disease in the acute phase, acute cardiovascular and metabolic diseases, neoplasia active in the previous five years, use of anti-inflammatory drugs, presence of neurological sequelae, fractures or surgical osteosynthesis in the last six months, and severe visual and hearing difficulties will be the criteria for exclusion. These diseases or comorbidities will be researched from the patient's medical records at the geriatric outpatient clinic, where they will be followed up and investigated by a screening instrument.

**Risks:**

Tests such as gait speed when walking, standing up and sitting from a chair can increase the heart rate and arterial pressure, cause fatigue, and mild to moderate dyspnea; however, these are normal signs during submaximal effort. These signs will be carefully monitored to ensure they remain within safe limits; the examiner will discontinue the test if there is a risk to the participant. If the participant is not able to continue the test or in the face of any extreme discomfort, the participant will be allowed to ask for discontinuation of the test.

The group of seniors who will undergo resistance muscle training with weight lifting, might feel muscle fatigue at the end of the exercise series; however, this feeling will be continuously monitored by a trained and experienced physiotherapist, and interruption will be allowed if the fatigue is intense. During resistance training there might be a slight increase in blood pressure, heart rate, and respiratory rate, which are normal signs indicative of moderate physical exertion; however, these signs should return to baseline values after a few seconds of effort. In case of any other signal or symptom that represents a risk of any adverse effect, the training will be discontinued and the participant will be monitored and advised rest until his or her prompt recovery.

Electro-stimulation can cause a slight tingling sensation, but without much discomfort. In case of cramps or muscular pains this will be immediately interrupted. Thus, the risks are minimal. Participants will be assisted by experienced and trained professionals and researchers, to avoid any intercurrence associated with the study procedures. In the event that a participant does not achieve prompt recovery, Mobile Emergency Care Service (SAMU) may be triggered.

The risks related to the use of the research project's questionnaires include exposure to the routine, recalling some stressful events such as tiredness and fear of falling when performing some activities, or discomfort over the time spent in filling out the questionnaire. These are minimal, but potential stressors. In case of a feeling of undue stress, the participant will be allowed to stop filling out the instruments at any time and will also be allowed to exit from participating in the survey. The interviews for filling the questionnaires will be conducted in a private environment, with the researcher being present with the subject in an individualized room for data collection. Researchers also guarantee the confidentiality and anonymity of the participants. The data will be presented only in averages for each group. No individual data will be revealed.

**Benefits:**

This study will help to determine whether electro-stimulation exercise of the entire body is as effective as resistance exercise (of lifting weights). Thus, participation by volunteers in this research might help in selecting the choice of treatment to improve the strength, muscle mass, and physical capacity of elderly people with sarcopenia who have a high risk of falls and physical disability. The treatment can improve the quality of life for such people. The advantage of this study is that if the effectiveness of electro-stimulation over resistance training is proven, it saves the time required for the process of physical training, because electro-stimulation requires less time than resistance training. Thus, this form of training can provide greater tolerance and increase the adherence among the elderly sarcopenic patients.

**Data analysis methodology:**

**Statistical analysis**

SPSS version 20.0 will be used. The data will be presented as average and SD or median and interquartile. Statistical analysis by intention to treat will be performed using the unpaired t-test or Mann-Whitney test. The effect size will be determined for each variable of interest. Analysis of mixed models, including the outcomes measured at the 4 time points (basal, immediately after intervention, and at 3 and 6 months) will be performed. The "time point" will be included as a class variable. Group, time, and group * time interactions will be inserted. This will evaluate the sole effect of the intervention, since the difference from baseline values at each time point will be evaluated. A value of p = 0.05 will be assumed for all tests.

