
**Summary:**

The high prevalence of sarcopenia in the elderly and the role of exercise training in reversing it is well-known. However, there are several limitations that prevent the elderly from adhering to a regular physical training program to increase the muscle strength or mass and to reduce the risk of falls. Recently, whole-body electrostimulation has been reported to be effective for recovery from sarcopenia, with a short period of intervention. This study aims to evaluate the effectiveness of whole-body electrostimulation in improving the function, and muscle strength and mass in the elderly, as well as in reducing their fear of falling and increasing social participation, compared to conventional resistance training. The subjects will be elderly people, with no cognitive and neurological impairment, and no acute or chronic diseases or musculoskeletal ailments that prevent them from performing resistance exercise. The sample will be randomized to two groups. The electro-stimulation group will undergo 18 minutes of electrical stimulation of the muscles, two sessions a week, for eight weeks. The regimen will be an intermittent bipolar electric current with a frequency of 85 Hz, pulse width of 350 μs, with 6 seconds of stimulation and 4 seconds of rest. The resistance training group will perform exercises with a load of 50 to 80% of 1-RM in supervised sessions, twice a week, over a period of 8 weeks. Muscle strength will be evaluated by Microfet manual dynamometer; functional evaluation will be determined by gait speed, TUG test, and sit-up test; muscle mass will be evaluated by electrical bioimpedance, questionnaires will be used to evaluate the fear of falling and degree of social participation. The intergroup data will be compared by paired t-test or Mann-Whitney test according to the tested normality. Longitudinal evaluations after 3 and 6 months of training will be conducted through questionnaires, to evaluate the degree of social participation and the fear of falling. The effect size will be determined for each variable of interest. Analysis of mixed models, including the outcomes measured at the 4 time points (basal, after intervention, 3 and 6 months) will be performed. It is expected that the results of this study will determine the effectiveness of whole-body electrostimulation in improving the functional capacity of the elderly and in reducing the risk of falls.

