**Procedures and Instruments:**

This will be a randomized, prospective, clinical trial to be conducted in the Laboratory of Movement Analysis of the Federal University of Juiz de Fora School of Physical Therapy. The subjects will be invited for participation by publicizing the study through posters at the university, personal communication, and dissemination through the internet and social networks. Participants will be informed and guided about the evaluations and objectives of the research, and those agreeing to participate will be asked to sign a Free and Informed Consent Terms. The evaluations will be initiated only after participants sign the Informed Consent Term. Participants will be instructed to wear comfortable clothing and appropriate footwear, and will be advised not to perform strenuous exercises at least 24 hours before the assessment and the exercise sessions. The allocation to the experimental and control groups after the baseline evaluation will be at random, using a table of random numbers.

All participants will be subjected to the evaluations described below, at baseline, immediately after the intervention, and eight weeks after the intervention. Questionnaires to evaluate the fear of falling and degree of social participation will also be administered at the same time points. The baseline assessment as well as re-evaluation after eight weeks of intervention will last approximately 40 minutes each. After the first re-evaluation, the subjects will be monitored at intervals of 3 and 6 months through the questionnaires about degree of social participation and fear of falling. These will be done through phone calls and will assess whether the effect of the training has been maintained over a year. The call for answering the questionnaire will last a maximum of 15 minutes, which will be the average response time for both questionnaires (Table 2).

Screening: The Screening Instrument (ANNEX 1) will be used to collect the data about demographic (e.g. age, gender) and clinical characteristics (medications, co-morbidities, clinical history, and family history).

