**Primary outcome:**

Changes in muscle strength of extensors of the knee, walking speed, number of repetitions in the sit-leave test, and change in the lean mass in kilograms.

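### The primary outcomes get only a two-sample test, called paired in one section and unpaired in another and chosen by a normality test; a single ANCOVA per outcome would be fixed in advance and more precise at no cost

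*Protocol*

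**What the plan says.** The Statistical analysis section of the protocol states: "Statistical analysis by intention to treat will be performed using the unpaired t-test or Mann-Whitney test". It names no baseline covariate and does not say whether the test is applied to changes or to post-intervention values.

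The Summary describes the same comparison differently: "The intergroup data will be compared by paired t-test or Mann-Whitney test according to the tested normality".

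The primary outcomes are listed as follows, the last of them in kg: "Changes in muscle strength of extensors of the knee, walking speed, number of repetitions in the sit-leave test, and change in the lean mass in".

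A second analysis is planned: "Analysis of mixed models, including the outcomes measured at the 4 time points", namely baseline, post-intervention and months 3 and 6. Its terms are given as "Group, time, and group * time interactions will be inserted", and it is said to isolate the intervention effect "since the difference from baseline values at each time point will be evaluated".

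On what is collected at months 3 and 6, Procedures and Instruments says that "the subjects will be monitored at intervals of 3 and 6 months through the questionnaires about degree of social participation and fear of falling". Table 2 agrees: its follow-up column contains only FES-I and LIFE-H, which are the secondary outcomes.

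**The concern.** Three things follow from these passages.

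- **The two descriptions of the test conflict.** The arms are formed by randomising different people, so there are no pairs between them. A paired t-test across arms is invalid, and it contradicts the Statistical analysis section.
- **The compared quantity is not fixed in advance.** A t-test addresses a difference in means and Mann-Whitney a shift in ranks. If a normality test decides, the four primary outcomes could be reported on different footings, settled only after the data are seen. This matters here because the Hypothesis section aims to show that the two trainings perform alike. Such a claim rests on an estimated difference and its confidence interval on a known scale.
- **The primary outcomes get the less efficient method.** The model that uses the repeated measurements is worded for outcomes that only the questionnaires satisfy. Strength, walking speed, chair stands and lean mass are left with a two-sample test, although each has a baseline value that could be used as a covariate.

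At stake is precision on every primary outcome in a trial of 33 per arm.

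**Working it through.** **Step 1: which outcomes can enter the four-time-point model.**

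| Outcome | Baseline | Post | Month 3 | Month 6 |
|---|---|---|---|---|
| Knee-extensor strength, walking speed, chair stands, lean mass (primary) | yes | yes | no | no |
| FES-I, LIFE-H (secondary) | yes | yes | yes | yes |

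This is Table 2. Procedures and Instruments also mentions an evaluation eight weeks after the intervention, which Table 2 does not show. Even with it, the primary outcomes would have three time points, not four. As worded, the model therefore fits only the secondary outcomes.

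**Step 2: the plan's own figure.** The sample size is 66, or 33 per arm. It cannot be reproduced, because no effect size, SD, power or dropout rate is given. Solving backwards (two-sided 0.05, 80% power, no dropout), 33 per arm corresponds to a standardised difference of about 0.69 to 0.70.

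**Step 3: variance under the three possible analyses.** Let σ² be the variance of a single measurement, assumed equal at baseline and post, and r the baseline-to-post correlation. The variance factors per participant are:

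- post values only: σ²
- change score: 2(1−r)σ²
- ANCOVA: (1−r²)σ²

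The ratios are:

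- ANCOVA to change = (1−r²)/(2(1−r)) = (1+r)/2
- ANCOVA to post-only = 1−r²
- equivalent size per arm against the change score = 33/((1+r)/2)

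| r (assumed) | ANCOVA / change | Equivalent per arm instead of 33 | ANCOVA / post-only |
|---|---|---|---|
| 0.5 | 0.75 | 33/0.75 = 44.0 | 0.75 |
| 0.7 | 0.85 | 33/0.85 = 38.8 | 0.51 |
| 0.8 | 0.90 | 33/0.90 = 36.7 | 0.36 |

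At r = 0.9 the gain over the change score shrinks to 5%. These ratios ignore the small cost of estimating the slope, which for 66 participants inflates the ANCOVA variance by about 1/(66−4) = 1.6%.

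**Step 4: what this means for power.** Assume a true difference of 0.5 SD of the post value, 33 per arm, two-sided 0.05 and complete data.

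| r (assumed) | Post-only | Change | ANCOVA |
|---|---|---|---|
| 0.5 | 53% | 53% | 65% |
| 0.7 | 53% | 75% | 81% |
| 0.8 | 53% | 90% | 92% |

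At r = 0.7, the unstated choice between post values and changes alone moves power by 75 − 53 = 22 percentage points. ANCOVA is at least as good as either at every r shown.

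**Step 5: would extending the mixed model be enough?** Suppose the model were also fitted to the baseline and post values of the primary outcomes, with group, time and their interaction. With two time points and complete data, the interaction is the difference in mean changes. That is the change-score comparison again, so the (1+r)/2 gain would still be available.

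**The case against.** The strongest reply is that little is actually wrong. *Paired* is probably a drafting slip, since the same sentence speaks of groups and names Mann-Whitney, an independent-samples test, and the dedicated statistics section says unpaired. The normality rule appears only in the Summary. That the mixed model excludes the primary outcomes is an inference, since no sentence restricts it to questionnaires. A change-score comparison is unbiased under randomisation.

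Much of this stands. The contradiction is cured by one word, and the rest concerns precision and pre-specification rather than bias. It does not remove the point. The two sections still disagree. The Statistical analysis section offers both tests and gives no other rule for choosing. The natural reading of the model's scope leaves the primary outcomes outside it.

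Two stronger readings are tempting and are not supported.

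- A reader might infer that the measured baseline is thrown away. The Primary outcome section defines changes, so baseline enters by subtraction. The ratios of 0.51 and 0.36 apply only if the test is run on post values.
- A reader might infer that the planned test cannot give an intention-to-treat analysis. A t-test by allocated arm is intention to treat when outcomes are complete, and nothing in the protocol says that dropouts are excluded by design. Rules for missing post values may be in a SAP that is not shown, so their absence here is no defect.

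**Conclusion.** The point holds as a contradiction to be corrected and an improvement that costs nothing. The Summary's paired test is invalid for independent arms and conflicts with the Statistical analysis section. The choice by normality test leaves the compared quantity open. The primary outcomes have no baseline-adjusted model.

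The size depends on r, which the protocol does not give. If changes are tested, as the outcome definition implies, ANCOVA cuts the variance by 25%, 15% and 10% at r = 0.5, 0.7 and 0.8. If post values are tested, the cuts are 25%, 49% and 64%. Both sets assume equal baseline and post variances.

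A reader might also expect the remedy to settle the intention-to-treat question. It does not: ANCOVA of the post value omits participants without one, just as a t-test does. A baseline-and-post mixed model is not equivalent to it on that point, and participants with baseline only would add little to the contrast after treatment. The label here means analysis by allocated arm.

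**What to change.** 1. In the Summary, change paired to unpaired so that it agrees with the Statistical analysis section.
2. For each primary outcome, make the main analysis one ANCOVA of the post-intervention value on arm and baseline value, by allocated arm. Report the adjusted difference with its 95% confidence interval.
3. State which assessment supplies the post-intervention value, since Procedures and Instruments and Table 2 differ on the schedule.
4. Remove the choice by normality test and keep Mann-Whitney as a sensitivity analysis only.
5. State that the four-time-point mixed model is for FES-I and LIFE-H, and that intention to treat means analysis by allocated arm. Leave the handling of missing post values to the SAP.

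The cost is wording only. No additional data or participants are needed, and the analysis runs in the software already named. Adjustment for sex and robust standard errors are optional and not part of this point.

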**Secondary outcome:**

Changes in fear of falling assessed by FES-I/Brazil and social participation by Life-H.

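### The four-time-point mixed model subtracts baseline at a fixed slope of 1 for FES-I and LIFE-H; a baseline-adjusted contrast would be more precise at almost no cost

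*Protocol*

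**What the plan says.** The Statistical analysis section of the protocol plans a mixed model whose response covers four time points: baseline, immediately after the intervention, month 3 and month 6. Time is categorical. The fixed effects are given as "Group, time, and group * time interactions will be inserted". The section argues that this isolates the effect of the intervention, "since the difference from baseline values at each time point will be evaluated". It names no baseline covariate and does not constrain the arms to a common baseline mean.

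The section does not say which outcomes this model serves; the schedule settles that. Procedures and Instruments limits the later contacts to two instruments: "the subjects will be monitored at intervals of 3 and 6 months through the questionnaires about degree of social participation and fear of falling". Table 2 likewise lists only FES-I and LIFE-H at months 3 and 6. These are the secondary outcomes, defined as "Changes in fear of falling assessed by FES-I/Brazil and social participation by Life-H".

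On the order of events, Procedures and Instruments states: "The allocation to the experimental and control groups after the baseline evaluation will be at random, using a table of random numbers". The Sample Size section plans 66 participants, 33 per arm.

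**The concern.** A free group term together with a free group-by-time interaction gives each arm its own baseline mean. Reading the effect as difference from baseline then takes the whole observed baseline gap off the follow-up gap. Because baseline is measured before random allocation, the true arm means at baseline are equal and any observed gap is chance. The follow-up gap carries forward only a fraction of that chance gap, namely the baseline-to-follow-up correlation (rho) when the SDs are equal. Subtracting all of it over-corrects.

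At stake is the precision of the between-arm estimates for fear of falling and social participation after training and at months 3 and 6. The Hypothesis section expects electrostimulation to be as effective as resistance training, so the width of the confidence interval matters directly for what the trial can say.

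**Working it through.** **Inputs from the protocol.** 33 per arm (Sample Size); a 0.05 level (Statistical analysis; two-sided assumed, as the protocol does not say); four time points, with group, time and group-by-time terms; baseline before allocation.

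**Inputs assumed.** The protocol gives no rho, SD, effect size or dropout. Its sample size therefore cannot be reproduced. For orientation, 33 per arm corresponds to (1.960 + 0.842) × √(2/33) = 0.69 SD at 80% power in an unadjusted two-sample comparison (normal approximation). Below, the outcome SD is 1 at each time, rho is 0.5, 0.7 or 0.8, and the true difference for the power figures is 0.5 SD.

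**Step 1: what the planned contrast estimates.** The model was fitted, with a random intercept, to one simulated complete data set (33 per arm, four times, rho 0.6).
- With baseline as the reference time, the group term equalled the observed baseline difference: 0.2926 by both routes.
- The three group-by-time terms equalled the raw differences in mean change: −0.0126, −0.1834 and −0.1916 by both routes.
- Holding the arms to one baseline mean moved the estimates to 0.096, −0.075 and −0.083 and reduced the standard error from 0.199 to 0.180.

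**Step 2: variances per participant, in SD² units.**
- Change: 2(1 − rho).
- Baseline-adjusted: 1 − rho².
- Ratio, adjusted to change: (1 − rho²) / [2(1 − rho)] = (1 + rho)/2.
- Narrowing of the confidence interval: 1 − √[(1 + rho)/2].

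**Step 3: numbers at 33 per arm.** Standard error = √(variance × 2/33). Power is from the non-central t with 64 df, two-sided 5%, for an assumed 0.5 SD difference.

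| rho | Variance, change | Variance, adjusted | Ratio | SE, change | SE, adjusted | CI narrower by | Power, change | Power, adjusted |
|---|---|---|---|---|---|---|---|---|
| 0.5 | 1.00 | 0.75 | 0.75 | 0.246 | 0.213 | 13% | 52% | 64% |
| 0.7 | 0.60 | 0.51 | 0.85 | 0.191 | 0.176 | 8% | 73% | 80% |
| 0.8 | 0.40 | 0.36 | 0.90 | 0.156 | 0.148 | 5% | 89% | 92% |

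To match the adjusted precision of 33 per arm, the change contrast would need 33/ratio: 44, 39 or 37 per arm.

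**Step 4: simulation check.** In 8,000 two-time-point trials per rho with a true difference of 0.50, both estimators averaged about 0.50. The variance ratio was 0.77 at rho 0.5 and 0.85 at rho 0.7. The first is slightly above theory because the slope has to be estimated. The change estimate correlated with the chance baseline difference at −0.49 (rho 0.5) and −0.39 (rho 0.7), close to the theoretical −√[(1 − rho)/2] = −0.50 and −0.39. For the adjusted estimate the correlation was within 0.01 of zero.

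**Step 5: size of the over-correction.** The standard error of the baseline difference is √(2/33) = 0.246 SD, so a gap beyond 0.25 SD in either direction arises by chance in about 31% of trials. A gap of 0.25 SD shifts the change estimate by (1 − rho) × 0.25, which is 0.125 SD at rho 0.5 and 0.05 SD at rho 0.8.

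**The case against.** The strongest reply is that the plan is valid as written. Allocation is random and follows baseline, so the difference in change is unbiased and keeps its type I error. The model and the endpoint definition agree, since the secondary outcomes are defined as changes. A preference for another valid model could be called taste. The validity part stands, and it limits the point to efficiency. It does not remove the gain, which comes from data the trial already collects.

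It also stands that the size rests wholly on assumed values. At rho 0.8 the gain is modest, and it vanishes as rho approaches 1. Power to detect a difference is an awkward yardstick for a hypothesis of similar effectiveness; interval width is the better one.

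Two qualifications also hold. Equality with raw change is exact only with complete data; with missed telephone follow-ups a likelihood-based fit departs from the observed change scores. And covariates are often left to a statistical analysis plan. Here, though, the protocol itself states the fixed effects and the contrast, so this is a stated choice rather than a gap.

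A reader might also infer that the Group main effect would be reported as the treatment effect, diluted because it averages over the baseline time. The protocol does not support this: it points to the difference from baseline at each time point, not to the Group term.

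**Conclusion.** The point holds as a matter of precision. For FES-I and LIFE-H the stated model and contrast give, with complete data, the between-arm difference in mean change. At assumed rho of 0.5 to 0.8 that contrast has confidence intervals which adjustment would narrow by about 13% to 5%, and it reacts to chance baseline imbalance where an adjusted contrast does not. The figures assume equal SDs over time, complete data and 33 per arm analysed; the power figures also assume a 0.5 SD difference.

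Three stronger readings should be resisted. Baseline is not ignored: it is subtracted, with the slope fixed at 1 rather than estimated. The contrast is not biased, because randomisation makes the expected baseline difference zero. And no primary conclusion is touched, since the schedule has none of the primary outcomes at months 3 or 6. The change is worth making because it is nearly free, but its reach is two secondary outcomes.

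**What to change.** Amend one sentence of the Statistical analysis section, choosing one of two forms:
- keep all four time points in the response but hold both arms to a common baseline mean, using time plus group-by-post-baseline-time terms (no separate group term) and an unstructured covariance; or
- model the three post-baseline values, with the baseline score and its interaction with time as covariates.

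In either case, name FES-I and LIFE-H as the outcomes of this model, and report the adjusted between-arm difference with its confidence interval at post-intervention, month 3 and month 6.

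The change needs no new data, visits or participants; both forms are standard mixed models. The one small downside is that the reported effect becomes a baseline-adjusted difference rather than a raw difference in change. Mean changes by arm can still be shown descriptively.

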**Sample Size:**

It is expected that 66 elderly people will be involved in the study, 33 in each arm. However, to understand the size of the effect, a pilot study with 10 subjects will initially be conducted to confirm our forecast based on the sample calculation.

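### The month 3 and 6 calls are meant to show whether the training effect was maintained, but the only contrast the protocol names is the difference from baseline, which does not address retention of the week-8 level

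*Protocol*

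**What the plan says.** Protocol, Procedures and Instruments, on the period following the week-8 assessment: "the subjects will be monitored at intervals of 3 and 6 months through the questionnaires about degree of social participation and fear of falling". The calls "will assess whether the effect of the training has been maintained over a year". No other purpose is given for them. Table 2 confirms that FES-I and LIFE-H are the only measures taken at those visits, and the protocol lists both as secondary outcomes.

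Protocol, Statistical analysis: a mixed model is planned, "including the outcomes measured at the 4 time points (basal, immediately after intervention, and at 3 and 6 months) will be performed". On its form: "The 'time point' will be included as a class variable", and "Group, time, and group * time interactions will be inserted". The section says this isolates the effect of the intervention, "since the difference from baseline values at each time point will be evaluated". The decision rule is "A value of p = 0.05 will be assumed for all tests".

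The protocol names no comparison of month 3 or 6 with the end of training. It gives no tolerable loss and no rule for calling an effect maintained.

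**The concern.** Whether an effect was maintained is a question about follow-up relative to the end of training. The null hypothesis of the named contrast is that the month 3 or 6 mean equals the baseline mean, that is, that nothing is left. Rejecting it shows that something is left, which is compatible with full retention and with the loss of most of the gain. Failing to reject it does not show loss either, because a modest gain that is fully kept can miss significance against baseline.

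Between arms, a baseline-referenced contrast at month 6 combines how much each arm gained with how much it kept. At stake is the durability statement, which is the stated reason for the calls. The primary outcomes are not measured at these visits and are untouched.

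**Working it through.** **Inputs from the protocol.** "It is expected that 66 elderly people will be involved in the study, 33 in each arm"; alpha 0.05. The protocol gives no effect size, SD or correlation for FES-I or LIFE-H, so it has no figure of its own to reproduce here.

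**Assumptions.** Normal scores with SD 1 at each visit; equal correlation rho between visits, 0.5 to 0.8; two-sided tests; no dropout; within-arm gain E at week 8 of 0.3, 0.5 or 0.8 SD, with half left at month 6. A gain means a change in the favourable direction.

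**Step 1: within-arm test of month 6 against baseline.**

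- SD of a change = sqrt(2(1 - rho)); SE = SD / sqrt(33).
- SE at rho 0.5: 1.000 / 5.745 = 0.174. At rho 0.8: 0.632 / 5.745 = 0.110.
- Noncentrality = (E/2) / SE; critical t on 32 df = 2.037.
- Example, E = 0.5: 0.25 / 0.174 = 1.44 gives 29%; 0.25 / 0.110 = 2.27 gives 60%.

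| Gain at week 8 | rho 0.5 | rho 0.6 | rho 0.7 | rho 0.8 |
|---|---|---|---|---|
| 0.3 SD | 13% | 15% | 19% | 26% |
| 0.5 SD | 29% | 34% | 44% | 60% |
| 0.8 SD | 61% | 70% | 82% | 94% |

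These are probabilities that a half-lost effect is still significant against baseline. They are power against a false null, since half the gain really is there, so they should not be compared with 5%.

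**Step 2: the opposite error.** A gain that is fully kept has noncentrality E / SE. For 0.3 SD, the month-6 test against baseline is non-significant in 61% of trials at rho 0.5 and 25% at rho 0.8. For 0.5 SD at rho 0.5 the figure is 20%.

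**Step 3: between arms.** Let one arm have means 0, 0.9, 0.7, 0.5 and the other 0, 0.5, 0.5, 0.5 over the four visits, 33 per arm.

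- Month 6 minus baseline: the true difference is 0, so the test rejects at 5%, as it should.
- Month 6 minus post-intervention: the true difference is 0.4 SD. Noncentrality is 0.4 / (sqrt(2(1 - rho)) x sqrt(2/33)) = 1.62 at rho 0.5 and 2.10 at rho 0.7, giving power of 36% and 54%.
- Planned group-by-time test (3 df): the arm differences 0, 0.4, 0.2, 0 have mean 0.15 and centred sum of squares 0.0225 + 0.0625 + 0.0025 + 0.0225 = 0.11. Noncentrality is (33/2) x 0.11 / (1 - rho) = 3.63 and 6.05, giving power of about 32% and 51%.

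The interaction test picks up the differing profiles almost as often as the targeted contrast. It does not say whether the difference arose in the gain or in the retention.

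**Step 4: precision of the missing contrast.** The within-arm 95% CI half-width for month 6 minus post-intervention is 2.037 x SE: about 0.35 SD at rho 0.5 and 0.22 SD at rho 0.8. Take an effect that is truly fully kept and a limit fixed in advance at a loss of 0.25 SD (half of a 0.5 SD gain). At rho 0.5 the CI excludes that loss in 29% of trials. With a limit of 0.40 SD (half of 0.8 SD) it does so in 61%. The arithmetic is that of Step 1 with the limit in place of E/2.

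**The case against.** The strongest reply is that nothing in the protocol restricts the model to baseline comparisons. With time categorical and a group-by-time term, the week-8 to month-3 and month-6 changes can be estimated from the same fit. The sentence on baseline differences can be read as a reason for the model and not as a closed list, and a full list of contrasts commonly belongs in the SAP, which is not at hand. This stands in part. A reader might infer that the model can evaluate only change from baseline, and the document does not support that. But the protocol does name and justify one contrast, and that contrast does not answer the question set for the calls. A SAP that simply followed it would carry the mismatch forward.

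A reader might also infer that a half-lost effect would often be reported as maintained. The protocol has no rule that equates significance against baseline with maintenance, and the frequency depends on inputs it does not give. At 0.3 SD, and at 0.5 SD with lower correlation, a half-kept effect is more likely to look lost.

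A third tempting reading is that a difference in retention between the arms would go unseen. Step 3 does not bear this out: the planned interaction test responds to the scenario, and the arms also differ by 0.4 SD at week 8. What remains is that neither result isolates retention.

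Finally, maintenance appears in one procedural sentence, not among the listed objectives or outcomes. That limits the weight of the point but does not remove it.

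**Conclusion.** The point holds in a limited form. The stated purpose of the month 3 and 6 calls and the only named contrast do not match, and no criterion for maintenance is given. It concerns FES-I and LIFE-H, both secondary.

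If a significant month-6 difference from baseline were read as maintenance, a half-lost effect would pass in 13% to 94% of trials across the assumed gains of 0.3 to 0.8 SD and correlations of 0.5 to 0.8. The width of that range shows how little can be said without the missing inputs. The figures assume normal scores, equal correlations, 33 analysed per arm and two-sided 5% tests. The mismatch itself rests on none of these, only on the two sections read side by side.

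**What to change.** Keep the mixed model as planned. In the Statistical analysis section, for FES-I and LIFE-H:

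- Add month 3 minus post-intervention and month 6 minus post-intervention within each arm, and the between-arm difference in these changes, each with a 95% CI.
- Keep the baseline contrasts, labelled as effect still present versus baseline.
- Allow the word maintained only if the CI excludes a loss fixed in advance in scale points. Half of the observed gain is not such a limit, because it is estimated from the same data. If a fraction of the gain is preferred, test a contrast that carries the uncertainty of the gain, for example (month 6 minus baseline) minus half of (post-intervention minus baseline).
- Do not take a non-significant change from post-intervention as evidence of maintenance.
- If no limit is agreed, report the estimated change and its CI without a maintenance claim.

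The cost is a few sentences and a few extra contrasts from a model already planned; no new data or participants are needed. The real downside is precision. With a within-arm half-width of about 0.22 to 0.35 SD, a firm maintenance claim will often be out of reach, and the protocol should say so beforehand.
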